## Plan of analysis

### Preliminary analyses

We will use the IBM SPSS Statistics 26 program for statistical analysis. In the
first step, we will clean the dataset and exclude participants with missing data
on any of the measurement points and within questionnaires, with more than 20%
of missing values. We will also perform basic psychometric analyses of the
questionnaires, namely the factor or other appropriate analyses to evaluate the
internal structure of the questionnaires and analysis of reliability as internal
consistency (coefficient α) and calculate the scores in accordance with the
scoring instructions.

In the next step, we will perform basic descriptive analyses (means and standard
deviations) and check the assumptions of the chosen statistical tests (such as
the normality of the distribution assumption). This step will be followed by
inferential tests, whereby results with a *p*-value below .05
will be considered statistically significant.

### Analyses of patient-related outcomes

The impact of CDSS use on the first patient-related outcome, that is health
quality measures (H2), will primarily be analyzed with growth curve
analyses.

The impact of CDSS use on the second patient-related outcome, that is perceived
quality of life (H3), will primarily be analyzed with repeated-measure analysis
of variance (ANOVA), with time as the within-subjects factor (T1 and T2; see
Figure 1).
Significant results will be followed up with pairwise post-hoc tests using the
correction to adjust for multiple testing. All results will be accompanied by
effect sizes.

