## Abstract

Although clinical decision support systems (CDSSs) are increasingly emphasized as
one of the possible levers for improving care, they are still not widely used
due to different barriers, such as doubts about systems’ performance, their
complexity and poor design, practitioners’ lack of time to use them, poor
computer skills, reluctance to use them in front of patients, and deficient
integration into existing workflows. While several studies on CDSS exist, there
is a need for additional high-quality studies using large samples and examining
the differences between outcomes following a decision based on CDSS support and
those following decisions without this kind of information. Even less is known
about the effectiveness of a CDSS that is delivered during a grand round routine
and with the help of socially assistive humanoid robots (SAHRs). In this study,
200 patients will be randomized into a Control Group (i.e. standard care) and an
Intervention Group (i.e. standard care and novel CDSS delivered via a SAHR).
Health care quality and Quality of Life measures will be compared between the
two groups. Additionally, approximately 22 clinicians, who are also active
researchers at the University Clinical Center Maribor, will evaluate the
acceptability and clinical usability of the system. The results of the proposed
study will provide high-quality evidence on the effectiveness of CDSS systems
and SAHR in the grand round routine.

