**Figure 1. fig1-20552076221129068:**
[figure not shown]
Study design.

At the enrollment (T1), patients will fill out the baseline questionnaires
collecting patient demographic information, and assessing their perceived
quality of life. The perceived quality of life is again measured at the end of
the intervention (T2).

Each patient will be followed for three–five days, depending on the standardized
care. During this period, health care quality measures, including health quality
measures, blood pressure, oxygenation and heart rate, and pain, are collected
for both groups two times a day. Blood pressure, oxygenation, and heart rate are
measured in all in-patients, recorded daily (standard procedure) and recorded on
a progression chart. In the intervention group, blood pressure, oxygenation, and
heart rate measures are stored electronically and the CDSS is used to flag
deviations from the standard, and alert the treating clinician. In the control
group, the standard progression chart is used as per hospital protocol. The
treating clinician is autonomous to decide to step up or modify antihypertensive
treatment. Pain is measured in all in-patients on daily basis, two times a day
(standard procedure), and recorded on a progression chart. In the intervention
group, the pain level is stored electronically and CDSS is used to flag and
alert the treating clinician on pain levels identified above anticipated. In the
control group, the standard progression chart is used as per hospital protocol.
The treating clinician is autonomous to decide to step up or modify analgetic
treatment.

The participating clinicians will be asked to evaluate the clinical usability and
provide answers on their acceptance of the CDSS system five times during the
study (after the first iteration, after half a year, after the first year, after
a year and a half, and after the last iteration).

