Additionally, we also performed calculations using the G*Power software.
Patient-related analyses will predominantly be based on the ANOVA repeated
measures statistical test with the within-between interaction (two groups, two
measurements). As we hypothesize a small effect size
(*f* *=* 0.10) and intend to use a
conventional significance threshold and power (α = 0.05, 1-β = 0.80), the total
sample size needed to detect the effects is 200 participants.

The clinicians will be included in the study with the within-subjects design,
whereby they will fill out the questionnaires five times during the study
period. As such, we performed the sample size calculation in the G*Power
software, choosing the Repeated Measures ANOVA test as the statistical test,
entering a medium effect size (*f* = 0.25), and choosing a
conventional significance threshold and power (α = 0.05, 1-β = 0.80). Such
calculations suggest that at least 21 clinicians must be recruited overall.

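### The H3 test is described with time only while the trial is sized on group-by-time; align the two, and adjust T2 for the T1 score, which is more precise at no extra cost

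*Protocol article*

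**What the plan says.** The protocol article describes the H3 analysis in two places.

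- *Analyses of patient-related outcomes*: quality of life is to be analysed primarily by a repeated-measures analysis "of variance (ANOVA), with time as the within-subjects factor (T1 and T2; see" Figure 1). Neither arm nor an arm-by-time term is mentioned. The next sentence begins: "Significant results will be followed up with pairwise post-hoc tests using the", and goes on to a correction for multiple testing.
- *Participants and recruitment*: the patient analyses are said to rest mainly on the repeated-measures ANOVA "measures statistical test with the within-between interaction (two groups, two" measurements). With f = 0.10, two-sided alpha 0.05 and power 0.80, the "sample size needed to detect the effects is 200 participants".

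Three other statements bear on the point. The Abstract says that quality of life will be compared between the two groups. The text under Figure 1 has patients complete the quality-of-life questionnaire at enrolment (T1) and again at the end of the intervention (T2), so a baseline score is collected. *Study design* says that the vascular and thoracic cohorts will be reported separately; *Participants and recruitment* gives 100 patients to each.

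**The concern.** There are two linked issues.

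First, the sentence that specifies the H3 test does not name the effect on which the trial was sized. In these patients the time effect is the change from enrolment to the end of a surgical stay. It carries no information on the decision support system. *Analyses of clinicians-related outcomes* uses almost the same form of words for the clinicians, who have no comparison arm, so the H3 sentence on its own does not distinguish a two-arm analysis from a one-sample one.

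Second, once the interaction is taken as the intended test, it is a less precise choice than the data allow. With two arms and two times it reduces to comparing mean change between arms. That fixes the coefficient of the T1 score at 1, whereas ANCOVA estimates it. The loss matters most for the separate cohort reports, each on half of the patients for whom power was calculated.

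The follow-up tests add a smaller point. In a two-by-two layout the interaction has one degree of freedom, so no further test is needed to locate it. The pairwise comparisons available include T1 versus T2 within each arm, and those are not randomised comparisons.

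**Working it through.** **Inputs.** From *Participants and recruitment*: f = 0.10, alpha = 0.05, power 0.80, two groups, two measurements, N = 200, 100 per ward. Not stated, and assumed here: 1:1 allocation, equal SDs at T1 and T2 (set to 1), no dropout. The T1–T2 correlation rho is not stated either; it is recovered in step 1 and then varied.

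**Step 1: reproduce the plan's figure.** For the within-between interaction with m = 2 measurements, the noncentrality is lambda = f² × N × m / (1 − rho), with 1 and N − 2 degrees of freedom. At rho = 0.5:

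lambda = 0.01 × 200 × 2 / 0.5 = 8, giving power 0.804.

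N = 200 is the smallest even total reaching 0.80 at rho = 0.5. Other correlations do not give it: rho 0 needs 396, 0.3 needs 278, 0.6 needs 160 and 0.7 needs 120. So the stated 200 implies rho = 0.5.

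**Step 2: translate the effect size.** In a two-by-two layout f = d/4, where d is the arm difference in mean change in SD units. So d = 4 × 0.10 = 0.40. At rho = 0.5 the change score has variance 2(1 − 0.5) = 1. A normal-approximation two-sample calculation with difference 0.40 and SD 1 gives 99 per arm, 198 in total, which agrees with 200.

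**Step 3: compare the two analyses.**

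- Change score: variance factor 2(1 − rho).
- ANCOVA of T2 on T1: variance factor 1 − rho².
- Ratio: (1 − rho²) / [2(1 − rho)] = (1 + rho)/2, so the reduction is (1 − rho)/2.

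At rho = 0.5 the ratio is 0.75. A simulation of 20,000 trials gave 0.743.

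**Step 4: power for d = 0.40.** For ANCOVA, lambda = d² × N / [4(1 − rho²)], with N − 3 denominator degrees of freedom. At rho = 0.5 and N = 200, lambda = 0.16 × 200 / (4 × 0.75) = 10.67, giving power 0.90.

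| rho | Variance reduction | N = 200: change → ANCOVA | N = 100: change → ANCOVA |
|---|---|---|---|
| 0.3 | 35% | 0.66 → 0.84 | 0.39 → 0.55 |
| 0.5 | 25% | 0.80 → 0.90 | 0.51 → 0.63 |
| 0.7 | 15% | 0.95 → 0.98 | 0.72 → 0.79 |
| 0.8 | 10% | 0.99 → 1.00 | 0.88 → 0.91 |

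At rho = 0.5, ANCOVA reaches 80% power with 150 patients, against 200 for the interaction.

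**Step 5: relax the equal-SD assumption.** With SDs S1 and S2, change-score variance minus ANCOVA variance is S1² + S2² − 2·rho·S1·S2 − S2²(1 − rho²) = (S1 − rho·S2)². This is never negative. It is zero when S1 = rho·S2, for example when rho = 0.5 and S1 is half of S2.

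**The case against.** The strongest reply is that the article, read as a whole, does plan an arm comparison. The Abstract promises one, the sample-size section names the interaction and the two groups, and the H3 paragraph opens by referring to the impact of the system's use. It calls time the within-subjects factor, not the only factor. This stands. A reader might infer from the H3 sentence alone that the trial will test time and never compare the arms; the documents do not support that. What remains is a wording mismatch between two sections.

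A reader might also infer that only ANCOVA tests the arm effect. That is wrong too. Under randomisation the interaction is a valid and direct test of the arm difference in change, and at rho = 0.5 it meets the stated 0.80 target with 200 patients. The advantage of ANCOVA is precision.

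The size of the gain can be challenged as well. No correlation is given, 0.5 is only implied by the sample size, and nothing supports equal SDs across a surgical stay. This stands as a reason to give a range in place of a single 25%. It does not reverse the direction, since the difference in step 5 cannot be negative.

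Finally, the post-hoc tests follow only significant results, are corrected for multiplicity, and could include the between-arm contrast at T2. The article nowhere says that an arm effect will be read from significance in one arm and not in the other. That is a possible misuse, not a stated rule.

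**Conclusion.** The point holds as a mismatch to reconcile and an efficiency improvement, not as an invalid analysis. The H3 sentence should name the arm comparison on which the trial was sized. Replacing the change-score equivalent with ANCOVA would cut the variance of that comparison by (1 − rho)/2, from 35% down to 10% over rho 0.3 to 0.8. At the implied rho of 0.5 this moves power from the planned level to about 0.90 overall. It also improves the position within each ward, although 0.63 there is still short of 0.80. These figures rest on the assumptions listed with the inputs; with unequal SDs the gain may be larger or smaller, down to zero. Since *Measures* calls quality of life a secondary objective and the planned interaction is valid, the change is advisable but its absence would not undermine the trial.

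**What to change.** In *Analyses of patient-related outcomes*, state the H3 test as a linear model of the T2 EQ-5D score on arm and T1 score. Fit it within each cohort, as the separate reporting in *Study design* requires, and add ward as a term in any pooled analysis. Report the adjusted arm difference with its 95% CI as the H3 result. State that within-arm T1 versus T2 post-hoc tests will not be used to infer an arm effect.

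If the repeated-measures ANOVA is kept, the minimum change is to name arm and the arm-by-time interaction in that section, so that it matches the sample-size section.

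The cost is a change of wording. The T1 score is already planned for every patient, and neither the sample size nor the visit schedule is affected.

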### Analyses of clinicians-related outcomes

Clinicians’ acceptance of the CDSS and its perceived clinical usability (H1) will
be analyzed with two separate repeated-measure ANOVA, with time as the
within-subjects factor. Significant results will be followed up with pairwise
post-hoc tests using the correction to adjust for multiple testing. All results
will be accompanied by effect sizes.

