^ Furthermore, the newly developed CDSS will provide intuitive visualizations
of patients’ health-related data, including EHRs, health quality measures (i.e.
pain, blood pressure, oxygenation, and heart rate), patient-reported data, and
patient-reported outcomes. The health data will be structured in an interoperable
HL7-FHIR format.^
31
^ The real-time access during the grand round routine is ensured with
speech-enabled user interfaces delivered via a tablet attached to the socially
assistive humanoid robot (SAHR), Pepper.^
32
^ While the uptake of SAHR in clinical practice is so far limited,^
33
^ and to our best knowledge, there are no studies on the integration of CDSSs
and social robotics yet, such innovative delivery could have several important
benefits. In particular, it could make the use of a CDSS more effortless for
clinicians (e.g. due to the robot being capable of movement, carrying the tablet,
and offering assistance with queries in natural language) as well as more
satisfactory and engaging for all involved stakeholders including
patients.^34,35^ It could serve as an enabler of real-time querying and
visualization of patient data.^
36
^ Adding human characteristics to the CDSS could contribute to higher trust in
the system.^33,37,38^

We hypothesize that clinicians will accept the CDSS and recognize its clinical
usability (H1). The use of CDSS will have a positive impact on health quality
measures (H2) and the quality of life of patients (H3). In addition to our primary
hypotheses, we aim to explore the impact of real-time access to the extended
clinical background on diagnostic and treatment workflows for patients with vascular
and thoracic diseases and conditions (R1).

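### H1 is about the level of clinician acceptance and usability, but its only planned test is of change over time, so the test cannot show whether H1 is true

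*Protocol article*

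**What the plan says.** The Introduction words H1 as a statement covering both acceptance and usability: "We hypothesize that clinicians will accept the CDSS and recognize its clinical". The Measures section ties the primary hypotheses to clinician usability and acceptance, and describes the patient outcomes as the secondary objective.

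Usability is measured with the SUS. Acceptance is measured with a study-specific questionnaire built on UTAUT and UTAUT2, still to be defined. Under Study design (text after Figure 1), clinicians rate usability and are also to "provide answers on their acceptance of the CDSS system five times during the" trial. The earliest rating follows the opening iteration, and the other four come at half-yearly steps, the last of them when the study ends. The first rating therefore comes after the system has been used.

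Under Analyses of clinicians-related outcomes, the two scores are to "be analyzed with two separate repeated-measure ANOVA, with time as the" repeated factor. If the time effect is significant, comparisons between pairs of assessments follow, with a multiplicity correction; effect sizes are reported throughout. No other inference for H1 is named.

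The sample size uses the same test. Participants and recruitment describes G*Power "software, choosing the Repeated Measures ANOVA test as the statistical test", a medium effect of *f* = 0.25, α = 0.05 and power 0.80. These "calculations suggest that at least 21 clinicians must be recruited overall". The Abstract expects about 22.

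**The concern.** The null hypothesis of a repeated-measures ANOVA on time is that the mean is equal at all assessments. H1 concerns where the mean lies. The two are unrelated:

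- Uniformly high ratings give a non-significant result although H1 is true.
- Uniformly poor ratings also give a non-significant result although H1 is false.
- A collapse in ratings over two years gives a significant result.

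Nothing else in the design fills the gap. Every rating comes from a clinician who uses the system, so there is no comparator. There is no rating before first use, so change cannot be read as the effect of introducing the system. The article gives no threshold for either score. The p < .05 rule under Preliminary analyses therefore applies, for H1, only to change. The Discussion names low user acceptance as a plausible reason for slow uptake and promises credible evidence; on this question the planned p-value cannot supply it.

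**Working it through.** **1. The stated sample size.** From Participants and recruitment: f = 0.25, α = 0.05, power 0.80. From Study design: m = 5 assessments, one group. Not stated, so assumed: correlation between assessments ρ = 0.5 and sphericity ε = 1.

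Noncentral F for a within-subjects effect:

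- λ = f² · N · m · ε / (1 − ρ)
- df1 = (m − 1)ε
- df2 = (N − 1)(m − 1)ε

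| N | λ | df1, df2 | Power |
|---|---|---|---|
| 20 | 0.0625 × 20 × 5 / 0.5 = 12.5 | 4, 76 | 0.793 |
| 21 | 0.0625 × 21 × 5 / 0.5 = 13.125 | 4, 80 | 0.816 |

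The smallest N with power of at least 0.80 is 21, as stated. The sample is sized to detect change over time. The figure depends on the assumptions: with ε = 1, N is 40 at ρ = 0, 28 at ρ = 0.3 and 13 at ρ = 0.7; with ρ = 0.5, N is 25 at ε = 0.75 and 33 at ε = 0.5. None of this affects what the test is about.

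**2. What the time test responds to.** Simulation with N = 21, five assessments, ρ = 0.5 and 20,000 runs per scenario. Scores are in SD units around an arbitrary zero. The trend is linear with f = 0.25.

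| True pattern | Rejection rate |
|---|---|
| Constant at +2 SD | 4.9% |
| Constant at −2 SD | 5.1% |
| Rising, around −2 SD | 81.7% |
| Falling, around −2 SD | 82.0% |
| Rising, around +2 SD | 81.7% |

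The first two rows are the nominal α, as they must be when the mean is constant. The level of the scores has no influence on the result, and neither does the direction of the trend.

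**3. What a level-based analysis could deliver with the same clinicians.** The documents give no SD or criterion, so results are in SD units of the score analysed.

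- 95% CI half-width for a mean, n = 22: t(0.975, 21)/√22 = 2.080/4.690 = 0.44 SD.
- Two-sided one-sample t-test at α = 0.05, 80% power: the true mean must lie about 0.63 SD from the criterion with n = 22, or 0.64 SD with n = 21.
- Power at n = 21: 26% at 0.3 SD, 59% at 0.5 SD, 81% at 0.65 SD, 94% at 0.8 SD.
- If each clinician's five scores are averaged and ρ = 0.5, the SD of that average is √[(1 + 4 × 0.5)/5] = 0.775 of a single-assessment SD. The half-width is then 0.44 × 0.775 = 0.34 single-assessment SD.
- Preliminary analyses excludes anyone missing a measurement point. With 15 completers, for illustration, the half-width is t(0.975, 14)/√15 = 2.145/3.873 = 0.55 SD.

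**The case against.** The strongest reply is that the level will be visible. Means and standard deviations are planned, and the pairwise comparisons will show whether a significant change is a rise or a fall. Nothing in the article says that a significant time effect will count as support for H1. This is right as far as it goes: H1 will be described, and a careful reader would notice a decline. It does not make the description a test. Without a criterion fixed in advance, almost any mean can be called acceptance afterwards, and most easily for a questionnaire not yet written.

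A second reply is that a cut-off could sit in a statistical analysis plan that is not shown. The absence of a number alone would indeed be no finding. The article, however, names this ANOVA as the analysis of H1 and sizes the sample for it. That is a stated choice, and it does not match the hypothesis.

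Third, the flaw leaves the randomised patient comparison untouched, and even a corrected analysis remains a single-arm rating. Both points stand. They limit the reach of the problem, but H1 is primary on either reading: Measures singles out the clinician outcomes, and the Introduction calls H1 to H3 together primary.

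Finally, H1 might mean growing acceptance. Its wording does not say so, and if that is intended the hypothesis needs rewording.

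**Conclusion.** The concern holds. Followed exactly, the plan yields a p-value about change that carries no information on whether clinicians accept the system or find it usable. It rejects at about 5% under constant scores whether these are high or low, and at about 82% under a trend of the planned size in either direction. The mismatch follows from the wording of H1 and the named test and needs no numerical assumption; the 82% and the reproduction of 21 assume ρ = 0.5 and ε = 1. The precision and power figures for a level-based analysis are best cases, because they assume complete data from 21 or 22 clinicians over two years. This must be fixed, because a primary hypothesis has no test of its truth.

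**What to change.** Before first use of the system:

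1. State a minimum acceptable mean for the SUS score and for one named acceptance score. For the study-specific questionnaire this could be a point above the scale midpoint, set once the items are final.
2. Name the assessment at which H1 is judged, or specify the average over all five.
3. Declare H1 supported only if the lower 95% confidence limit exceeds the criterion for both scores, since H1 claims both.
4. Keep the repeated-measures ANOVA and post-hoc tests as a secondary description of trend.
5. Restate the clinician sample size as precision: 0.44 SD of the score analysed with 22 complete responders (about 0.34 single-assessment SD for the five-assessment average if ρ = 0.5), with a range for fewer completers.

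If the investigators mean that acceptance will change over time, the alternative is to reword H1 that way, with the direction given, and to drop the claim about level.

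The cost is analysis-plan wording. Questionnaires, schedule and recruitment stay as they are. The only real commitment is to a threshold in advance.
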